### 3.2 Exclusion criteria

- At screening, severe obstructive lung disease with FEV1.0 <60% of predicted, or severe restrictive lung disease with total lung capacity (TLC) <60% of predicted; or pulmonary hypertension due to lung disease (Group 3 pulmonary hypertension) judged by the principal or subinvestigator to adequately explain the pulmonary hypertension.
- At screening, severe valvular disease of the aortic valve or mitral valve, or left ventricular ejection fraction (LVEF) <40% on transthoracic echocardiography; or pulmonary hypertension due to left heart disease (Group 2 pulmonary hypertension) judged by the principal or subinvestigator to adequately explain the pulmonary hypertension.
- Poorly controlled tachyarrhythmia (resting heart rate >100 bpm).
- Diagnosis of acute symptomatic pulmonary embolism on imaging within 3 months prior to registration.
- Congenital or acquired abnormalities of pulmonary vascular anatomy or course.
- History of lung resection or radiotherapy to the chest.
- Active thoracic malignancy.

- History of vasculitis.
- Presence of devices in the chest (e.g., pacemakers or implantable cardioverter-defibrillators) for which pulsed X-ray imaging may be contraindicated and/or that may interfere with dynamic chest radiography and image analysis.
- Women who are pregnant, or women of childbearing potential who are not using appropriate contraception.
- Any other condition judged by the principal or subinvestigator to make the patient unsuitable for participation in this trial.

### **3.3 Discontinuation criteria**

- Discontinuation judged necessary by the principal investigator (e.g., serious adverse events related to the investigational device, poor subject compliance).
- Request by the subject to discontinue participation.

## **4 Overview of the investigational device**

### **4.1 Regulatory classification of the investigational device**

- Category: diagnostic program (disease diagnosis program).
- Generic name: program for workstation for X-ray diagnostic imaging devices.
- Device class: Class II.
- Name of investigational device: Pulmonary Circulation Analysis Program.
- In this trial, we will use "PH2-MODE" installed on the "Diagnostic Imaging Workstation KONICA MINOLTA DI-X1" (Marketing authorisation certification No.: 230ABBZX00092000).
- Identification code: CTR340.

### **4.2 X-ray static/dynamic imaging system**

- A stationary digital general-purpose X-ray diagnostic apparatus, or a mobile digital general-purpose X-ray diagnostic apparatus.
- Product name: Diagnostic X-ray system RADspeed Pro (SHIMADZU Corp. Tokyo, Japan).
- Marketing authorisation certification No.: 221ABBZX00210000.
- Digital radiograph with flat panel detector output reading.
- Product name: Digital Radiography SKR 3000 (KONICA MINOLTA v Tokyo, Japan).
- Marketing authorisation certification No.: 228ABBZX00115000.
- Within the basic configuration: "DR panel".

## Clinical trial devices and other equipment used in the trial

In this trial, the clinical trial devices consist of the investigational device and approved imaging devices used to acquire and analyse dynamic chest radiography images. In addition, standard-of-care systems for lung ventilation–perfusion (V/Q) scintigraphy and image viewing are used.

### Clinical trial devices

Investigational device

- Name: Pulmonary Circulation Analysis Program (PH2-MODE) installed on the image diagnostic workstation “KONICA MINOLTA DI-X1” (Marketing authorisation certification No.: 230ABBZX00092000).
- Identification code: CTR340.

Other clinical trial devices (approved medical devices already installed at participating sites)

- X-ray static/dynamic imaging system (e.g., RADspeed Pro; SKR 3000; DR panel; image-processing controller).
- These devices will be managed and maintained in accordance with each participating site’s procedures and applicable regulations.

### Other devices used in the trial

- Lung V/Q scintigraphy imaging system: a rotating gamma camera SPECT system or SPECT/CT system used for routine clinical examinations at each participating site.
- Image diagnosis system (viewer): a nuclear medicine image-processing workstation and/or a general-purpose diagnostic image viewer. Images should be reviewed on a monitor that meets JIRA “JESRA X-0093\*B-2017” management grade 1A (maximum luminance  $\geq 350$  cd/m^2).

### System configuration and data flow

Dynamic chest radiography images are acquired by irradiating pulsed X-rays (15 frames per second) for a fixed duration (minimum 6 s to maximum 10 s) to generate a sequence of chest radiographs. The acquired dynamic images are submitted to the image interpretation committee via the upload system, analysed on the DI-X1 workstation using PH2-MODE (KONICA MINOLTA INC. Tokyo, Japan), and the resulting pulmonary circulation analysis images are transmitted to the diagnostic viewer for interpretation.

For V/Q scintigraphy, planar images, SPECT images, and (when available) CT images for fusion are acquired using the SPECT or SPECT/CT system. The images are submitted to the image interpretation committee via the upload system, processed on a nuclear medicine image-processing workstation, and transmitted to the diagnostic viewer for interpretation.

## Method for extracting pulmonary blood-flow information using the Pulmonary Circulation Analysis Program

As shown in Figures 6, pulmonary arterial blood volume changes with cardiac pulsation, which leads to temporal changes in pixel values in dynamic chest radiography images. The investigational device detects and visualises pulmonary blood-volume change from end-diastole by the following steps:

- Detect the time course of pixel values within a region of interest (ROI) placed over the heart,  $PV\_H(\text{frame})$ , and estimate the cardiac frequency  $f_0$  from  $PV\_H(t)$ .
- Detect the time course of pixel values within multiple ROIs placed in the lung fields,  $PV\_L(x, y, \text{frame})$ .
- Apply a band-pass filter that passes only the frequency band around  $f_0$  to  $PV\_H(\text{frame})$  and  $PV\_L(x, y, \text{frame})$  to remove signal components not related to cardiac pulsation; the filtered signals are denoted  $FPV\_H(\text{frame})$  and  $FPV\_L(x, y, \text{frame})$ .
- Detect the end-diastolic frame  $F_d$  from  $FPV\_H(\text{frame})$  (reference frame). For each frame, compute the change in the lung-field signal relative to the reference frame:

$$\Delta FPV\_L(x, y, \text{frame}) = FPV\_L(x, y, \text{frame}) - FPV\_L(x, y, F_d)$$

- Colour-code  $\Delta FPV\_L(x, y, \text{frame})$  for each frame using a predefined colour lookup table to generate a cine sequence (pulmonary circulation analysis movie: PH2-Dynamic).
- Generate a minimum intensity projection (MinIP) image from the cine sequence as a representative image (pulmonary circulation analysis summary image: PH2-Summary).

[figure not shown]

[figure not shown]

Figure 6. Operating Principles of the Pulmonary Circulation Analysis Program

## Input, output, and interpretation of the investigational device

### Input

Expected acquisition conditions for dynamic chest radiography

- Patient position and projection: supine anteroposterior (AP; recommended) or upright posteroanterior (PA).
- Breath-hold: 6–10 s (typically 7 s).
- Pulsed X-ray parameters: tube voltage and mAs are set according to the participant's BMI so that the signal-to-noise ratio of the dynamic images is maintained above a prespecified threshold as far as possible irrespective of body mass index.
- Frame rate: 15 frames per second.
- Image size: 17 × 17 in (424.8 × 424.8 mm; 1,062 × 1,062 pixels; 400 μm pitch) or 14 × 17 in (348.8 × 425.6 mm; 872 × 1,064 pixels; 400 μm pitch).

Rationale: In Protocol Version 3.0, upright PA acquisition was permitted. A previous report suggested comparable diagnostic performance between supine and upright acquisition for acute pulmonary embolism (Yamasaki et al., Eur J Radiol Open 2024;100602).

### Output

- $\Delta\text{FPV\_L}(x, y, \text{frame})$ : frame-by-frame change in the filtered lung-field signal relative to the reference frame.
- Note: a filter that passes only the frequency band around the cardiac cycle is applied in advance to extract pulsation-related signal changes.

- PH2-Dynamic: a colour-coded cine sequence generated by applying a predefined colour table to  $\Delta\text{FPV\_L}(x, y, \text{frame})$ .
- PH2-Summary: a representative image generated from PH2-Dynamic using minimum intensity projection (MinIP).

### Interpretation and handling of the output

- Regions with a small  $\Delta\text{FPV\_L}(x, y, \text{frame})$  appear darker on PH2-Dynamic/PH2-Summary.
- A small pulsation-related signal change around the cardiac frequency suggests a smaller pulsatile pulmonary blood-volume change compared with surrounding areas, and the region is interpreted as having relatively reduced pulmonary blood flow.
- Regions with a large  $\Delta\text{FPV\_L}(x, y, \text{frame})$  appear as deeper red to yellow on PH2-Dynamic/PH2-Summary.
- A large pulsation-related signal change suggests a larger pulsatile pulmonary blood-volume change compared with surrounding areas, and the region is interpreted as having relatively preserved or increased pulmonary blood flow.
- The output PH2-Dynamic and PH2-Summary images are interpreted by physicians together with the static chest radiograph. When no parenchymal abnormality is identified on the static chest radiograph and a region darker than the surrounding area is identified on PH2-Dynamic or PH2-Summary, that region is judged to have a perfusion abnormality.

## 5 Methods

### 5.1 Study design

This is a prospective, multicentre, assessor-blinded, case-wise randomised diagnostic performance study designed to verify the superiority of diagnostic accuracy for discriminating CTEPH from non-CTEPH when dynamic chest radiography/pulmonary circulation analysis is added to the standard initial work-up, compared with the standard initial work-up alone.

In this trial, the clinical positioning of the investigational device is as shown in the figure 7; the design aims to evaluate whether the addition of the pulmonary circulation analysis program to the initial work-up improves diagnostic performance for initial discrimination between CTEPH and non-CTEPH.

#### **Standard initial work-up (control) includes:**

- Blood tests (complete blood count; D-dimer; total protein; albumin; blood urea nitrogen; creatinine; uric acid; total bilirubin; AST; ALT; LDH; C-reactive protein; sodium; potassium; chloride; estimated glomerular filtration rate; NT-proBNP).
- Static chest radiography (e.g. conventional chest X-ray) (upright posteroanterior view is preferable).

- Resting 12-lead electrocardiogram.
- Pulmonary function tests (TLC measured value and % predicted; VC measured value and % predicted; FEV1 measured value and % predicted; FEV1/FVC%).
- Transthoracic echocardiography (peak tricuspid regurgitation velocity; cine images of parasternal short-axis B-mode and parasternal long-axis and apical four-chamber B-mode and colour Doppler).

Note: The duration of anticoagulant therapy is not restricted.

## **5.2 Informed consent, screening and registration**

Patients in whom pulmonary hypertension is suspected on transthoracic echocardiography may participate in this trial (see Section 3.1). The principal or subinvestigator will judge whether the patient is eligible. The physician will explain trial participation and obtain written informed consent. Initial work-up examinations (including blood tests, static chest radiography, electrocardiography, pulmonary function tests and echocardiography) will be performed within 28 days before registration (screening period). Initial work-up examinations may be performed on the same day as informed consent. After eligibility is confirmed following screening, the patient will be registered. Enrolment will end when 108 patients have been registered.

## **5.3 Dynamic chest radiography and V/Q scintigraphy**

After registration, dynamic chest radiography and V/Q scintigraphy will be performed within 28 days (the interval between the two examinations must be within 14 days).

### **5.3.1 Standards for acquiring dynamic chest radiography**

Dynamic chest radiography (DCR) images are acquired using a stationary digital general-purpose X-ray system capable of pulsed X-ray irradiation and a flat-panel detector-based digital radiography system. Figure 7 illustrates the recommended patient positioning for supine AP acquisition and highlights practical considerations to avoid truncation of the lung fields due to a short source-to-image distance.

[figure not shown]

**Figure 7. Overview of dynamic chest radiography acquisition and pulmonary circulation analysis.**

Dynamic chest radiography is performed using a pulsed X-ray generator and a flat panel detector while the patient holds their breath in the supine anteroposterior position (or upright posteroanterior position where applicable). Sequential X-ray images acquired during pulsed X-ray irradiation are transferred to a dedicated workstation, where the pulmonary circulation analysis program processes the image series to generate dynamic and summary perfusion-surrogate images. Representative examples of patient positioning for dynamic chest radiography are shown.

The steps from image acquisition to generation of pulmonary circulation analysis images are summarised in Table 5. All steps are performed by radiologic technologists.

| Step | Description                                                                                                                                                                                                                                                                                                                                                                                                                                                                                                                                                                                                                                                                                                                                                                                                                                                                                                                                                                                                                                                                                                                                                                                                                                                        |
|------|--------------------------------------------------------------------------------------------------------------------------------------------------------------------------------------------------------------------------------------------------------------------------------------------------------------------------------------------------------------------------------------------------------------------------------------------------------------------------------------------------------------------------------------------------------------------------------------------------------------------------------------------------------------------------------------------------------------------------------------------------------------------------------------------------------------------------------------------------------------------------------------------------------------------------------------------------------------------------------------------------------------------------------------------------------------------------------------------------------------------------------------------------------------------------------------------------------------------------------------------------------------------|
| 1)   | 
Acquire a static chest radiograph (CXR) and dynamic chest radiography (DCR).
 
 
• CXR: X-ray exposure parameters are set according to body mass index (next table). Patient position and projection are aligned with those used for DCR.
 
• DCR: X-ray exposure parameters are set so that the signal-to-noise ratio of the dynamic images is maintained above a prespecified threshold as far as possible irrespective of body mass index. Patient position/projection: supine AP (recommended) or upright PA. Breath-hold: 6–10 s (typically 7 s). Image size: 17 × 17 in (424.8 × 424.8 mm; 1,062 × 1,062 pixels; 400 µm pitch) or 14 × 17 in (348.8 × 425.6 mm; 872 × 1,064 pixels; 400 µm pitch). Signal-value dynamic range: 16-bit (0–65,535). Pulse repetition frequency: 15 Hz for all participants.
 
• Procedure: Position the participant appropriately. When acquiring in the supine position, note that a shorter source-to-image distance may narrow the irradiation field; confirm that the lung fields are not excluded. Confirm that the irradiation field covers the entire panel. Perform a practice breath-hold, then acquire DCR according to the breath-hold protocol.
 
 |
| 2)   | Visually confirm the acquired CXR and DCR. Exclude inappropriate images and                                                                                                                                                                                                                                                                                                                                                                                                                                                                                                                                                                                                                                                                                                                                                                                                                                                                                                                                                                                                                                                                                                                                                                                        |

|    |                                                                                                                                                                                                                                                                                                                                                                                  |
|----|----------------------------------------------------------------------------------------------------------------------------------------------------------------------------------------------------------------------------------------------------------------------------------------------------------------------------------------------------------------------------------|
|    | repeat acquisition when necessary.
Inappropriate image criteria: insufficient dose; body motion; marked rib motion; marked diaphragmatic motion (inadequate breath-hold); failure to secure the background ROI.                                                                                                                                                               |
| 3) | Transfer the CXR to the diagnostic viewer and transfer the DCR to the DI-X1 workstation on which PH2-MODE is installed.                                                                                                                                                                                                                                                          |
| 4) | On the DI-X1 workstation, use PH2-MODE (both KONICA MINOLTA INC. Tokyo, Japan) to automatically generate the pulmonary circulation analysis movie (PH2-Dynamic) and summary image (PH2-Summary). Confirm the following checkpoints (see the separate “Procedure for creating analysis images” for details): background ROI position; heart ROI position; and lung boundary line. |
| 5) | Visually confirm the pulmonary circulation analysis images and exclude inappropriate images.
Inappropriate analysis-image criteria: marked artefacts due to body motion; marked artefacts due to rib motion; marked artefacts due to inadequate breath-hold.                                                                                                                  |
| 6) | Finalise PH2-Dynamic and PH2-Summary on the DI-X1 workstation and transmit them to the diagnostic viewer.                                                                                                                                                                                                                                                                        |

Recommended pulsed X-ray irradiation conditions according to body mass index (supine AP projection)

| BMI category | Tube voltage (kV) | Tube current (mA) | Exposure time (ms) |
|--------------|-------------------|-------------------|--------------------|
| BMI<17       | 85                | 250               | 2.2                |
| 17≤BMI<20    | 95                | 250               | 1.8                |
| 20≤BMI<23    | 95                | 250               | 2.5                |
| 23≤BMI<26    | 95                | 250               | 3.2                |
| 26≤BMI<29    | 95                | 250               | 4                  |
| 29≤BMI<32    | 95                | 250               | 4.5                |
| 32≤BMI       | 95                | 250               | 5                  |

Recommended pulsed X-ray irradiation conditions according to body mass index (upright PA projection)

| BMI category | Tube voltage (kV) | Tube current (mA) | Exposure time (ms) |
|--------------|-------------------|-------------------|--------------------|
| BMI<17       | 85                | 80                | 8.0                |
| 17≤BMI<20    | 100               | 80                | 5.0                |
| 20≤BMI<23    | 100               | 80                | 6.3                |
| 23≤BMI<26    | 100               | 80                | 7.1                |
| 26≤BMI<29    | 110               | 250               | 2.2                |
| 29≤BMI<32    | 110               | 250               | 2.5                |
| 32≤BMI       | 110               | 250               | 3.6                |

CTEPH discrimination criteria (image interpretation committee): Determined in accordance with the SOP for image interpretation.

Six-region assessment of perfusion defects on pulmonary circulation analysis images (image interpretation committee): For each of the six lung regions, record “present” for regions judged to have embolic-type perfusion abnormalities and “absent” for regions judged not to have embolic-type perfusion abnormalities. Static chest radiography is not used for this six-region assessment (V/Q mismatch is not considered).

### **5.3.2 Six-region assessment of perfusion defects on perfusion scintigraphy**

For perfusion scintigraphy, technetium-99m macroaggregated albumin (99mTc-MAA) will be administered, and lung perfusion images will be acquired using a gamma camera SPECT system or SPECT/CT system. Multi-direction planar images (including anterior and posterior views; two views are acceptable) and SPECT images will be obtained; where available, CT images for fusion will also be acquired.

Six-region assessment (image interpretation committee): Using SPECT/CT (or SPECT when CT is unavailable) to define the cranio-caudal extent of the lungs, each lung will be divided into three equal zones (upper, middle and lower), resulting in six zones in total. A reference anterior planar image with six-zone division lines will be created for scoring. For each of the six zones, readers will record “present” when an embolic-type perfusion abnormality is judged to be present and “absent” when it is judged not to be present. Ventilation scintigraphy is not used for this six-region assessment; therefore, V/Q mismatch is not considered in this analysis.

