#### **7.1.3 V/Q scintigraphy / SPECT-CT**

For ventilation scintigraphy, krypton-81m gas or technetium-99m aerosol (gas) will be used; for perfusion scintigraphy, technetium-99m macroaggregated human serum albumin (99mTc-MAA) will be used. V/Q scintigraphy is obtained by imaging the lungs with a gamma camera with detectors positioned outside the body. The presence/absence of regional ventilation–perfusion mismatch will be evaluated and recorded. Multi-direction planar images (including anterior and posterior views; only two views are acceptable), SPECT images, and (where available) CT images for fusion will be acquired. For details, refer to “section 5.3 Evaluation of pulmonary perfusion impairment in each of six lung regions on perfusion scintigraphy”.

Obtained images will have personal information masked and will be submitted to the image interpretation committee.

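### Without fusion CT, the six-zone grid for the scintigraphic comparator is drawn from perfusion SPECT, so a complete apical or basal defect can shift the grid used to score it

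*Protocol*

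**What the plan says.** Section 5.3.2 builds the grid for the perfusion scintigraphy reading in three steps.

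- The lung extent is found "Using SPECT/CT (or SPECT when CT is unavailable) to define the cranio-caudal extent of the lungs".
- On that extent, "each lung will be divided into three equal zones (upper, middle and lower), resulting in six zones in total".
- The lines are transferred to a single template: "A reference anterior planar image with six-zone division lines will be created for scoring".

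The only acquisition described in Section 5.3.2 is the 99mTc-MAA perfusion study. The section adds that "Ventilation scintigraphy is not used for this six-region assessment; therefore, V/Q mismatch is not considered in this analysis". Read together, the SPECT named as the fallback is perfusion SPECT.

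The fallback can occur in practice. The section on other devices allows "a rotating gamma camera SPECT system or SPECT/CT system used for routine clinical examinations at each participating site", and Section 5.3.2 says only that "where available, CT images for fusion will also be acquired". The alt-FAS in Section 10.2.3 removes cases with missing or inappropriate perfusion images, but it does not name absence of CT as a reason for exclusion.

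The resulting scores are the comparator for the six-region kappa, a secondary endpoint in Section 5.7.2. Under Section 13.4, three nuclear medicine physicians read every case and the majority decides each region.

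**The concern.** Perfusion SPECT shows perfused lung. If a defect abolishes all uptake at a pole, that pole also drops out of the measured extent, so the grid depends on the finding that it is meant to locate. Fusion CT gives an anatomical outline, and SPECT alone gives a perfusion-dependent one. One endpoint is then built by two rules according to the equipment at the site.

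Majority voting does not correct this, because all three physicians score on the same lines. What is at stake is the six-region kappa. Some disagreement between the device and scintigraphy could come from misplaced lines and not from a difference in perfusion.

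**Working it through.** **Plan's own figures.** The protocol states no expected value, threshold or sample size for the six-region kappa. Its one design calculation, in Section 10.1, concerns the primary endpoint and reproduces. With accuracies 0.705 and 0.92, two-sided 5%, 80% power and pooled variance,

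n = [1.96·√(2·0.8125·0.1875) + 0.8416·√(0.705·0.295 + 0.92·0.08)]² / 0.215² ≈ 50.5, so 51 per group and 102 in total. Then 102/0.95 = 107.4, so 108. The grid does not enter this calculation.

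**Geometry.** Take lung height 1, measured downward from the apex, with a complete apical defect of depth d. The measured extent is 1 − d.

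- Upper/middle line: d + (1 − d)/3 = 1/3 + 2d/3, a shift of 2d/3.
- Middle/lower line: d + 2(1 − d)/3 = 2/3 + d/3, a shift of d/3.

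| d | upper/middle line | middle/lower line |
|---|---|---|
| 0 (anatomical) | 0.333 | 0.667 |
| 0.10 | 0.400 | 0.700 |
| 0.167 | 0.444 | 0.722 |
| 0.25 | 0.500 | 0.750 |
| 0.333 | 0.556 | 0.778 |

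A height d lies outside every drawn zone. For d up to 1/3, a further height 2d/3 + d/3 = d of perfused lung carries the wrong zone label. A basal defect gives the mirror image.

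**Conditions for an error.**

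1. The defect must remove all uptake at that level. Residual uptake leaves the extent unchanged.
2. If the image reader recognises the missing pole and assigns it to the nearest zone, the pole is scored correctly for d up to 1/3. Beyond that, the defect reaches a depth d − 1/3 into the true middle zone (0.067 at d = 0.40). Other defects near the moved lines can still be misplaced at any d.
3. Section 5.3.2 does not say whether the extent is set for each lung or for both together. A common extent would protect a one-sided defect.

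**Illustrative kappa.** None of these inputs is in the protocol: device sensitivity and specificity 0.90 per zone; edge-defect depth uniform on 0.08 to 0.30; up to two other defects per lung, each of height 0.10 to 0.25; 8,000 simulated lungs per setting, extent set per lung. The device is scored on anatomical zones. Each pair is the kappa against the anatomical grid, then against the grid as specified, pooled over cases with and without CT.

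| No CT | Lungs with edge defect | All edge defects missed | All recognised |
|---|---|---|---|
| 10% | 10% | 0.787 → 0.781 | 0.782 → 0.781 |
| 30% | 20% | 0.785 → 0.754 | 0.793 → 0.785 |
| 50% | 40% | 0.802 → 0.705 | 0.806 → 0.783 |

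The starting values differ slightly because of simulation error.

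**The case against.** The strongest reply is that the lines are only a scoring template. Experienced nuclear medicine physicians have multi-direction planar and SPECT images, and nothing tells them to ignore an absent apex or base. Complete loss of uptake at a pole may be uncommon, and the SOP for image interpretation, which is not shown, may already deal with it. Most of this stands as a limit on size. It does not remove the point, because Section 5.3.2 itself names the source of the outline, and recognising the pole does not put the inner lines back.

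Four stronger readings are tempting, and the protocol does not support them.

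- *Every edge defect at a site without CT is missed or put in the wrong zone.* This needs complete loss of uptake, and either a pole that goes unrecognised or one deeper than a third of the lung.
- *The kappa is biased downward by a known amount.* Neither the share without CT nor the defect frequency is given. The protocol also gives no rule for dividing the X-ray analysis image into six regions. The lung boundary line in the image-generation steps of Section 5.3.1 is a processing checkpoint, so anatomical zones on the device side are an assumption.
- *The kappa of 0.79 in Section 1.5 is the baseline for this endpoint.* It appears to be a patient-level figure. The accompanying agreement of 0.90 has interval 0.79–0.95. A Wilson interval for 0.90 is about 0.79–0.96 with 50 patients, but about 0.86–0.93 with 50 × 6 = 300 regions treated as independent. The simulated values near 0.79 follow from the assumed device accuracy.
- *The primary result is affected.* It compares the readers' initial discrimination with the investigator's diagnosis and does not use the grid.

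**Conclusion.** The point holds as a conditional weakness in how the comparator is measured. When fusion CT is unavailable, the rule as written lets a complete apical or basal defect shorten the measured lung, move both inner lines by 2d/3 and d/3, and leave the lost pole outside the drawn zones. The six-region kappa can be distorted, and it mixes two kinds of grid.

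The size cannot be determined from the protocol. Under the assumed inputs the pooled loss ranges from under 0.01 to about 0.10 (0.802 − 0.705 = 0.097), and the upper end requires half the cases without CT, 40% of lungs affected and every edge defect missed. If every one is recognised, the same setting loses about 0.02. The conclusion rests on reading SPECT in Section 5.3.2 as perfusion SPECT and on the extent being set for each lung. It concerns one secondary endpoint only. It is still worth correcting before reading begins, because suitable images are already collected.

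**What to change.** Amend Section 5.3.2 and the reading SOP as follows.

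1. When fusion CT is absent, set the lung outline from an already collected image that does not depend on perfusion, and say that perfusion SPECT is not used for this. Candidates are the ventilation images required by Section 7.1.3 ("For ventilation scintigraphy, krypton-81m gas or technetium-99m aerosol (gas) will be used"), the static chest radiograph, or an existing CT where there is one. If ventilation images are chosen, write an outline-only exception to the statement that "Ventilation scintigraphy is not used for this six-region assessment"; the scoring itself stays perfusion-only. CT cannot be the only fallback, because Section 5.4 accepts catheter angiography instead.
2. State that an unperfused apex is scored in the upper zone and an unperfused base in the lower zone, and whether the extent is set for each lung or for both together.
3. Report the six-region kappa also for SPECT/CT cases only.

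The cost is a few sentences, an extra outlining step for cases without CT, and slight misregistration between the outline image and the perfusion image in those cases. No new examination, image reader or patient is needed.
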